## Abstract

**Study Objectives:**

Insomnia is common in the general population and is diagnosed based on self-reported sleep complaints. There is a frequent discrepancy between objectively recorded and self-reported sleep (sleep–wake state discrepancy), especially in individuals with insomnia. Although sleep–wake state discrepancy is well-documented in the literature, it is not well understood. This protocol describes the methodology of a randomized control study, which will examine whether providing monitoring and feedback about objectively recorded sleep with support for interpretation of sleep–wake state discrepancy improves insomnia symptoms and will explore the potential mechanisms of change.

**Methods:**

Participants are 90 individuals with insomnia symptoms (Insomnia Severity Index [ISI] ≥10). Participants will be randomized to one of two conditions: (1) Intervention: feedback about objectively recorded sleep (actigraph and optional electroencephalogram headband) with guidance for data interpretation, (2) Control: sleep hygiene session. Both conditions will involve individual sessions and two check-in calls. The primary outcome is ISI score. Secondary outcomes include sleep-related impairment, symptoms of anxiety and depression, and other sleep and quality of life measures. Outcomes will be assessed using validated instruments at baseline and post-intervention.

**Discussion:**

With increasing number of wearable devices that measure sleep, there is a need to understand how sleep data provided by these devices could be utilized in the treatment of insomnia. Findings from this study have the potential to better understand sleep–wake state discrepancy in insomnia and uncover new approaches to supplement current insomnia treatment.

Statement of SignificanceNumerous wearable devices provide sleep data, but few provide feedback tailored to individuals with insomnia. Current insomnia treatments do not routinely utilize data from wearable devices. This adequately powered, randomized study could fill this gap by investigating whether providing monitoring and feedback about recorded sleep, with support for interpretation of sleep–wake state discrepancy, could improve insomnia symptoms. Findings have the potential to better understand sleep-state perception in insomnia and uncover new approaches to supplement current insomnia treatment.

## Introduction

Insomnia is characterized by dissatisfaction with sleep, including difficulty initiating or maintaining sleep, and/or early-morning awakenings [1], with associated daytime impairment such as fatigue and mood disturbances [2]. 9% to 30% of individuals in the general population experience symptoms of insomnia [3–6]. The diagnosis of insomnia disorder is based on self-reported sleep complaints, without the need for recorded sleep data [1, 7]. Individuals with insomnia often underreport total sleep time (TST), and overreport sleep onset latency (SOL; time to fall asleep) and wake after sleep onset [8–11] compared to recorded sleep. The difference between self-reported and objectively measured sleep parameters is known in the literature as sleep-state misperception [12–14], paradoxical insomnia [15–17], or sleep discrepancy [18–20]. In this manuscript, we will use the term sleep–wake state discrepancy [21] to define differences that occur when comparing objectively recorded versus self-reported sleep data.

Sleep–wake state discrepancy is a common phenomenon observed in 9%–50% of individuals with insomnia [22–26]; it has also been observed in other sleep disorders including sleep apnea [27–29], periodic limb movement disorder [26], narcolepsy [30], as well as adults in the general community [31–33]. Although sleep–wake state discrepancy may include longer or better perceived (vs. objectively measured) sleep (e.g. “reverse sleep state misperception,” [34] “positive sleep state misperception” [35]), shorter and poorer perceived sleep has been consistently linked to greater insomnia symptoms. For example, individuals with insomnia and higher sleep–wake state discrepancy self-report poorer sleep (i.e. lower sleep quality, shorter TST, longer SOL, and lower sleep efficiency) and higher insomnia symptom severity compared to those with lower sleep–wake state discrepancy [20].

The underlying mechanisms of sleep–wake state discrepancy are not well understood, but the potential perspectives can be grouped into the following categories: physiological aspects include local modulations of sleep depth (i.e. local sleep) and sensitivity to sleep fragmentation [36–41]. Measurement-related aspects include differences in how tools assess sleep, as each tool infers sleep in a different way (e.g. polysomnography from electroencephalogram signals, actigraphy from activity and movement) [21]. Cognitive-related aspects include sleep-related worries and selective monitoring [42, 43]. Harvey’s cognitive model of insomnia suggests that concerns and worries about sleep and associated daytime consequences could lead to increasing sleep monitoring, which can result in overestimating sleep difficulties [42]. Therefore, sleep-related thoughts and beliefs appear to play an important role in the perception of sleep and the development of insomnia.

Sleep–wake state discrepancy has been shown to be modifiable [16, 44, 45], and reducing it may improve sleep complaints. Downey et al. [46] provided individuals with insomnia feedback about their sleep via polysomnography (PSG) by waking them up 27 times per night. After feedback, participants more accurately estimated their sleep/wake state and reported an improved ability to fall asleep. Tang et al. [44] conducted a pilot study (*N* = 40), in which individuals with insomnia were randomly allocated into either “shown discrepancy” or “non-demonstration” groups. The “shown-discrepancy” group was taught to read actigraph data and calculate sleep–wake state discrepancy; subsequently, they reported shortened SOL and less anxiety and preoccupation about sleep compared to the “non-demonstration” group [44]. Tang et al. [45] expanded on those findings with another experiment (*N* = 48), in which the control condition was verbally told about sleep–wake state discrepancy without demonstration or calculation. Consistent with findings from the earlier study, those who completed the intervention had a greater reduction in self-reported sleep impairment, insomnia symptoms, and sleep-related anxiety and distress [45].

On the contrary, receiving “negative feedback” (e.g., being told that last night’s sleep was poor quality) about sleep may have adverse effects. For example, one study (*N* = 22) found that providing individuals with insomnia “negative” feedback about their sleep was associated with increased negative thoughts, sleepiness, monitoring for sleep-related threats, and daytime safety behaviors, relative to “positive” sleep feedback [47]. Similarly, a more recent study (*N* = 63) found that giving individuals with insomnia “negative” feedback about their sleep resulted in significantly lower self-reported alertness and significantly higher levels of self-reported sleepiness and fatigue compared to those given “positive” sleep feedback [48].

Cognitive behavioral therapy for insomnia (CBT-I), the first-line treatment for chronic insomnia [49–51], has also been shown to influence sleep–wake state discrepancy [20, 52–55]. Chan et al. [18] found that the behavioral components of CBT-I alone (i.e. stimulus control, sleep restriction, and sleep hygiene and relaxation) reduced SOL discrepancy in older adults compared to those in the self-monitoring control group. The cognitive components of CBT-I may also impact sleep as they reduce dysfunctional beliefs and attitudes about sleep (DBAS) [56–59], which is related to improvements in sleep–wake state discrepancy [60]. Although monitoring of self-reported sleep is an integral part of CBT-I, objective sleep measurements are not routinely employed in CBT-I. Conventional CBT-I also does not include a component of supporting individuals with insomnia in understanding sleep-state perception.

The consumer market is seeing increasing varieties of wearable devices that objectively record sleep. Additionally, an increasing number of individuals with insomnia are presenting to sleep services with personally recorded sleep history, with the expectation that clinicians can understand and utilize their data [61–64]. Most sleep wearables utilize actigraphy (e.g. Fitbit), and some models are found to be comparable to research-grade altigraphs when detecting sleep/wake measures [65, 66]. A small number of head-worn wearables (e.g. Dreem) record electroencephalogram (EEG) signals and calculate sleep stages [67]. Although these devices sometimes provide consumers with feedback about sleep duration and quality (e.g. brief sleep variable descriptions, calculated sleep scores with descriptions), most do not provide detailed guidance about how to interpret the data in relation to users’ own sleep experiences. Some devices provide comparisons of the user’s data with those in the general population, which in some cases might cause a perpetuation of sleep-related anxiety that leads to a perfectionistic sleep quest (i.e. orthosomnia) [68]. This guidance for meaningful interpretation of data are especially important for individuals with insomnia, where sleep discrepancy might be high, and the aforementioned literature shows that different sleep feedback may result in different symptom outcomes.

Therefore, this randomized controlled study utilizes two conditions: one condition provides feedback on wearable measured sleep variables and discusses sleep–wake state discrepancy, and the other (control) condition provides information about sleep hygiene. This study aims to: (1) Examine whether providing individuals with insomnia feedback about sleep using sleep wearable devices, along with support for interpretation of sleep–wake state discrepancy improves symptoms of insomnia as the primary outcome. It is hypothesized that providing monitoring and feedback will result in a significantly greater reduction in insomnia symptom severity from baseline to post-intervention compared to control. Group differences in the changes of sleep and mental health domains (e.g. symptoms of depression, anxiety, and sleep-related daytime functioning) are also explored given their potential associations with both sleep perception and insomnia symptoms [4, 69–73], and (2) Explore potential mechanisms of change, including sleep–wake state discrepancy (operationalized as the differences between self-report and wearable measured sleep variables), dysfunctional beliefs and attitudes about sleep, presleep arousal, and aspects of sleep architecture (e.g. increased percentage spent in non-rapid eye movement [NREM] and rapid eye movement [REM], reduction of NREM and REM fragmentation, and increase slow wave density and amplitude).

## Methods

This is a two-arm, parallel-group, single-blind, and superiority randomized study. The study is prospectively registered here https://anzctr.org.au/, ACTRN12619001636145. This protocol paper follows recommendations from the SPIRIT-PRO Extension (Standard Protocol Items: Recommendations for Interventional Trials—Patient-Reported Outcomes) guidelines [74] and the template for intervention description and replication checklist and guide [75].

### Participants

Participants will be 90 individuals with significant insomnia symptoms. Inclusion criteria will be: (1) age ≥18 years, (2) able to communicate in English, (3) have regular access to the internet, smartphone, and email, and (4) Score ≥10 on the insomnia severity index (ISI) [76]. Exclusion criteria will be: (1) undertaking current fixed night shift work between 12 am and 5 am or current rotating work schedules that require night shift during the study period, (2) significant symptoms of the following sleep disorders based on duke structures clinical interview for sleep disorders (DSISD) [77]: sleep apnea (loud snoring, or observed gasping or pauses in breathing, or previously diagnosed with an apnea hypopnea index >15 but not/inadequately treated), periodic limb movement disorder (previously diagnosed with an arousal index >15), restless legs syndrome (occurring 3 times per week with a duration of at least 1 month), irregular and non-24 hours circadian rhythm sleep–wake disorders (advanced if habitual bedtime is earlier than 8 pm and habitual wake time earlier than 4 am, occasional deviation allowed; delayed if habitual bedtime later than 3 am and habitual wake time later than 11am, occasional deviation allowed), (3) at risk determined by individuals who select either moderate or high on the suicidal ideation item on the baseline questionnaire, and (4) using sleep information on Fitbit or Dreem apps in the month prior to participation.

### Procedures

This study was initially designed to recruit individuals from the Monash University Healthy Sleep Clinic (MUHSC; Victoria, Australia) for a mixture of in-person (e.g. study orientation session) and remote (e.g. phone) contact. Due to the coronavirus (COVID-19) pandemic, contact with participants will be completely remote (e.g. videoconference) and we will supplement recruitment with individuals from the community.

#### Recruitment

This study is promoted as the “Novel Insomnia Treatment Experiment (NITE)” and the following community and online recruitment strategies will be utilized: (1) At MUHSC, we will send recruitment invitations to (1) current patients who report significant insomnia symptoms (score ≥10 on the ISI at the intake questionnaire or are referred by a sleep physician) and have consented to be contacted about future research opportunities, and (2) past patients who gave consent to be contacted about future research opportunities. (2) Study recruitment materials will be placed in the general community Australia-wide, these included relevant online forums, social media, sleep websites, podcasts, and flyers placed in appropriate public spaces (e.g. notice board).

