#### Telephone screening

The telephone screening will take about 30 minutes and will cover: DSISD [77], medication use, engagement with psychotherapy or sleep treatments, and a risk assessment. Individuals who meet exclusion criteria due to the presence of other sleep disorders will be encouraged to discuss their conditions with a health professional, with appropriate referrals being made whenever necessary. Individuals eligible for the study will be booked in for a study information session and are sent the baseline questionnaire.

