#### Ethics considerations

Ethics approval is obtained from the Monash University Human Research Ethics Committee (MUHREC; 20856). All participants will provide informed consent for their participation. The consent will clarify that the decision of whether or not to participate in the study will not affect usual care and that participants are free to withdraw from the study at any time. Participants excluded due to current psychiatric conditions or severe comorbid sleep disorders will be encouraged to speak to their doctor about their mental health and medical needs. Any changes to the study protocol will be reported to and approved by the MUHREC before being implemented and are updated on the prospective registration.

Each participant will be assigned identification. Participants’ identifiable information will only be stored in REDCap, which has role-based secure access, and researchers working on this project or staff at the MUHSC have different levels of access (e.g. full access, de-identifiable information only). Access can also be immediately revoked if required. No identifiable personal information will be stored outside of REDCap, participants are only identified by their numeric identification. Only researchers approved by the MUHREC and staff of the MUHSC can access REDCap to re-identify participants. Participant's personal information (e.g. name, phone number) will be flagged and removed by REDCap when being used for research and/or service evaluation purposes.

No later than 7 years after the final publication, we will de-identify the data by removing names, date of birth, addresses/contact details, and any information that may link the data to participants personally. These personally identifying data will be completely erased and destroyed. The de-identified database will be made publicly available through Monash Bridges (or comparable platform) to maximize the potential benefit to the scientific and research community. Additionally, each variable will be screened, and rare categories with <5 individuals will be collapsed prior to sharing. No data monitoring committee will be employed in the current study due to limited scale, nor will study auditing be undertaken.

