#### Statistical and power analysis

All analyses will be conducted on an intention-to-treat basis. Missing data is expected in this study design as participation occurs over several weeks and will be addressed using multiple imputations through chained equations. Pooled results from the multiply imputed data will be the primary analyses. Analysis will be conducted in R.

To examine group differences in primary and secondary outcomes, each outcome will be entered into a separate multiple regression model. Each outcome at post-intervention will be the dependent variable, with the outcome at baseline included as a covariate. Treatment conditions will be dummy coded and entered as the focal predictor. Stratification factors will be dummy coded and included as covariates in all models.

Each outcome will be evaluated for assumptions. If an outcome demonstrates substantial skew or non-normality, transformations (e.g. log, square root) will be evaluated to see if they improve normality. If outliers and extreme values are present, sensitivity analyses will use quantile regression to estimate the medians rather than linear regression as quantile regression models are less sensitive to extreme values. Scatter plots will be used to evaluate the association between each outcome at baseline and post-intervention. If there is evidence of substantial non-linearity, a generalized additive model will be used with a smooth term on the baseline outcome to allow non-linear associations.

In all cases, effect sizes will be calculated to quantify the size of group differences, 95% confidence intervals calculated around estimates of treatment group differences, and within-group change scores summarized to quantify the average change over time in each group. Sensitivity analyses will be conducted using only participants with complete data on each outcome. To explore predictors of treatment response, potential predictors will be incorporated in regression analyses as predictors or moderators.

Assuming an attribution rate of 20%, randomizing 90 participants in total (45 per group) will give the study 80% power (two-tailed *a* = 0.05, regression analyses) to detect a medium effect size (*d* = 0.6) on the ISI as the primary outcome. The effect size estimation is based on a previous behavioral intervention experiment, also included the ISI as the outcome, and addressed the discrepancy in self-report versus objective sleep information in individuals with insomnia [45].

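### Concurrent insomnia treatment is asked about at screening but used nowhere in the named design or model, and no record of non-drug treatment is scheduled afterwards

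*Protocol article*

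**What the plan says.** All references are to the protocol article.

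- **Who is invited.** Recruitment lists "current patients who report significant insomnia symptoms (score ≥10 on the ISI at the intake questionnaire or are referred by a sleep physician"), then past patients of the same clinic, then community volunteers across Australia.
- **Usual care.** Ethics considerations says the consent will make clear that "the decision of whether or not to participate in the study will not affect usual care".
- **Eligibility.** Participants gives four exclusions: night-shift work, other sleep disorders, suicide risk, and recent use of Fitbit or Dreem sleep information. None concerns current or newly started insomnia treatment.
- **What is asked before randomization.** Telephone screening covers "DSISD [77], medication use, engagement with psychotherapy or sleep treatments, and a risk assessment".
- **What is recorded later.** Table 1 schedules medication use at baseline (T1) and post-intervention (T2), and the daily diary includes sleep medication. Table 1 names no item on psychological or other non-drug sleep treatment at T2.
- **Stratification and model.** Randomization is stratified by baseline ISI only. Statistical and power analysis regresses the post-intervention score on arm and baseline score, and adds that "Stratification factors will be dummy coded and included as covariates in all models".
- **Link to the mechanism.** The Introduction calls cognitive behavioural therapy for insomnia (CBT-I) first-line treatment and says it "has also been shown to influence sleep–wake state discrepancy". That discrepancy is one of the candidate mechanisms in Aim 2. The intervention session leaves out key CBT-I components.

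**The concern.** The protocol screens out recent exposure to device sleep feedback and keeps key CBT-I components out of its own session. It has no corresponding step for CBT-I or other sleep treatment received elsewhere, although part of the sample comes from a sleep clinic. A participant in active treatment and an untreated volunteer may have quite different expected ISI courses over about 5 weeks. Three things follow:

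1. **Precision of the primary contrast.** Mixing treated and untreated participants widens the outcome distribution. A variable that could remove some of that spread is collected at screening and then left out of the named model.
2. **Treatment started after allocation.** Participants know their arm, so uptake of outside treatment could differ between arms. Unless it is a drug, no scheduled item would show it.
3. **Aim 2.** Change in discrepancy is not randomized. Outside treatment that moves both discrepancy and ISI could produce an association between them that the feedback did not cause.

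**Working it through.** **The plan's own figure.** The sample-size statement reads "Assuming an attribution rate of 20%, randomizing 90 participants in total (45 per group) will give the study 80% power". The test is two-sided at 0.05 and the target is d = 0.6 on the ISI. Reading the percentage as attrition, 45 × 0.8 = 36 completers per arm. With no baseline correlation, the normal approximation gives Φ(0.6 × √(36/2) − 1.96) = Φ(0.586) = 72.1%, and the noncentral t gives 70.9%. The stated 80% is reached in a regression if the baseline-post correlation is about 0.45, a value the article does not state. That is a separate question. Both 80% and 72% are carried below as starting points.

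**Assumed inputs, none of them in the documents.** Residual ISI SD is 5, so d = 0.6 is 3 points. Treated participants improve 6 points more in either arm. The treated share p is 10% to 30%. The feedback effect is the same 3 points in treated and untreated participants.

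**Added variance.** A two-group mixture adds p(1 − p) × 6² to the residual variance of 25. The effect size becomes 3/SD.

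| p | Added variance | Total variance | SD | d | Variance ratio to 25 |
|---|---|---|---|---|---|
| 0 | 0 | 25.00 | 5.00 | 0.600 | 1.00 |
| 0.1 | 0.09 × 36 = 3.24 | 28.24 | 5.31 | 0.565 | 1.13 |
| 0.2 | 0.16 × 36 = 5.76 | 30.76 | 5.55 | 0.541 | 1.23 |
| 0.3 | 0.21 × 36 = 7.56 | 32.56 | 5.71 | 0.526 | 1.30 |

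**In terms of power** (normal approximation, p = 0.1, 0.2, 0.3):

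- Starting from the stated 80%, Φ((1.96 + 0.842) × d/0.6 − 1.96) gives about 75%, 71% and 69%.
- Starting from 72.1%, Φ(d × √18 − 1.96) gives about 67%, 63% and 61%.

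**Chance imbalance is the same loss, not a second one.** At p = 0.2 with 45 per arm, the SD of the difference in treated share is √(2 × 0.16/45) = 0.084. Multiplied by 6 points, this is 0.51 ISI points. The standard error at SD 5 is 5 × √(2/45) = 1.05. Combining them, √(1.05² + 0.51²) = 1.17, which equals the standard error at the inflated SD, 5.55 × √(2/45) = 1.17. A figure for chance imbalance must not be added to the fall in d.

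**A different premise.** If treated participants gained only half of the feedback effect, with no added variance, d would be 0.6 × (1 − p/2) = 0.57, 0.54 and 0.51 at 10%, 20% and 30%. The loss is similar in size. This form is dilution of the average effect, and covariate adjustment would not recover it.

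**Parts without arithmetic.** For treatment started after allocation, and for Aim 2, the documents give nothing from which a size could be calculated.

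**The case against.** The strongest reply has four parts.

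- **The protocol does take some account of treatment.** Screening asks about it, medication is recorded twice and in the diary, and the analysis section allows potential predictors to enter as predictors or moderators. This stands: a reader who inferred that concurrent treatment is ignored would be wrong. But the predictor sentence is generic and exploratory, and it does not put treatment status into the primary model.
- **The ISI contrast is not biased.** Treatment present before randomization is balanced in expectation, and the standard error covers chance imbalance. This stands too. A reader might infer that a positive or null result could not be told apart from differences in background treatment. For treatment present at randomization, the design does not support that inference.
- **The passages can be over-read.** The usual-care sentence is consent wording and does not say that CBT-I is delivered during the trial. The intake ISI identifies current patients; it does not show that they are invited just as treatment begins. No treated share is given. All of this is accepted, and it is why the magnitude is only an illustration.
- **An article condenses.** Extra covariates may be in an analysis plan not shown, Table 1 does not show item content, and the content of the calls is only summarised. This carries some weight for the covariates. It carries less for the post-intervention record, because Table 1 is the stated measurement schedule and a later analysis plan cannot recover data that were never collected.

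A yes/no answer at screening would also miss someone about to start treatment. Recruitment source is a partial proxy for that, so the remedy is incomplete.

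**Conclusion.** The point holds as a modest loss of efficiency plus a gap in data collection. It is not a threat to the validity of the primary comparison. Treatment status is collected at screening and has no stated use in eligibility, stratification or the primary model, and non-drug treatment after screening has no scheduled record.

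Under the assumptions stated in the working, d falls from 0.60 to about 0.57-0.53, and this range already includes chance imbalance. If few participants are treated, or the extra improvement is smaller, the loss shrinks towards nothing.

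Two further consequences are possible but cannot be sized from the documents: differential uptake of outside treatment after unblinded allocation, and confounding of the mechanism analysis. The second bears only on Aim 2, which the protocol itself describes as exploratory.

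**What to change.** 1. Prespecify two baseline covariates in the primary ISI model and in the mechanism models: current psychotherapy or sleep treatment at screening (yes/no) and recruitment source (clinic v community). The first is already asked. The second should be known from the recruitment route; confirm that it is stored.
2. Add one question at T2 on any sleep or psychological treatment received since baseline. Report it by arm. Do not adjust for it in the primary model, because it is measured after randomization and could itself be affected by allocation.

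This changes no eligibility criterion and no aspect of participants' care.

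The cost is two degrees of freedom and one short questionnaire item. Adjustment recovers only the variance explained by status at screening and recruitment source. It does not address treatment started later or any dilution of the effect. The T2 question makes later treatment visible by arm, which helps readers judge the ISI result and the mechanism findings, but it does not remove the confounding in Aim 2. It has to be in place before post-intervention data are collected.
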